##### Intervention Component 2: Family Meetings for Parents

Within each class, children and parents are invited to two family meetings. The family meetings comprise a workshop for parents that combines education and dialogue between parents, while children engage in fun and interactive activities. The overall goal of these meetings is to support parents in fostering balanced and sustainable leisure habits, within the class community and at home, with particular attention to screen use. Building on empirical insights from the intervention development phase and inspired by theoretical perspectives such as social support theory [24], the meetings provide parents with a possibility to share experiences and foster dialogue, helping parents gain strategies and confidence to address digital challenges effectively. An essential aspect of the meetings is to foster collective decision-making on key issues relevant to the specific class, which could be (in)appropriate screen content, online gaming, or social media use. By aligning on these matters, the goal is to reduce social pressure, strengthen unity, and promote the development of more sustainable rules [25,26].

The first family meeting focuses on screen-related aspects within the family, while the second meeting addresses children’s screen use within the class. As part of the second meeting, data collected from the children during the curricular activities (Table 1) is presented to the parents to ground the discussions in the children’s real-life experiences and perspectives. Evidence-based knowledge is shared through slides referencing research and recent reports as well as videos featuring expert statements. In addition, handouts are provided to parents, including practical guidance on how to install parental controls on a child’s smartphone and how to initiate conversations about screen use within the family. Workshops are led by a trained facilitator provided by the project, and all materials are freely available online following the meeting.

Activities for the children are conducted by staff from the after-school club or sport science students from the University of Southern Denmark, coordinated by the research team in collaboration with the school, based on their preferences. These activities, along with a concluding shared dinner, are included as part of the intervention to support and encourage parent participation by making attendance as convenient as possible.

##### Intervention Component 3: Brief Exercise for Parents

In Denmark, a class-wide parent-teacher meeting is held at the beginning of each school year. During this meeting in 4th grade, parents take part in a brief teacher-led exercise focusing on screen media dilemmas. The primary goal is to raise awareness about the project and encourage parents to participate in the upcoming family meetings.

##### Intervention Component 4: Development Program for After-School Club Staff

The development program consists of 3 workshops conducted within the after-school club setting. The program is developed in collaboration with Ungdomsringen, which facilitates the program.

The development program is inspired by principles of action learning [27], applied in a condensed, iterative format referred to as a “mini action learning cycle.” This means that the after-school club staff are expected to develop their own practice based on specific, real-life challenges and dilemmas they have experienced. In this way, the issues addressed during the process are directly relevant to their everyday practice, supporting ownership of the change process.

During the workshops, after-school club staff are supported in investigating identified challenges and preparing small actions to be implemented in their everyday practice. In the following session, their experiences and observations become the basis for systematic reflection, knowledge sharing, and the development of new insights—insights that can inform further actions. As part of the program, the after-school club staff are introduced to knowledge, tools, and methods that enable them to continue developing their practice—even after the formal conclusion of the development program. The overall aim of the program is to increase participation in the after-school club and reduce dropout rates from 3rd to 4th grade. To achieve this, the program, for example, seeks to foster a shared understanding of current practices across key themes, and strengthen empowerment and a sense of unity among the club’s staff.

##### Intervention Component 5: Community Workshops for Local Stakeholders

The last intervention component comprises two 3-hour workshops in the local community. A local ambassador and 15‐18 local stakeholders are recruited from the local community, representing parents, schoolteachers, after-school club personnel, local politicians, and others relevant to children’s leisure time (representatives from, for example, local sports clubs, library, and church). With support from the research team, the local ambassador is responsible for planning the two workshops, which are led by trained facilitators. The workshops are based on the GMB methodology, aiming to foster a shared understanding of the problem by collaboratively developing a system dynamics model grounded in diverse stakeholder perspectives [28]. GMB has been shown to enhance problem understanding, strengthen stakeholder engagement and confidence in systems thinking, and foster consensus for action [23,29,30]. Based on experiences from the feasibility study and the fact that the local workshops are part of a multicomponent intervention, the decision was made to limit the workshop component to two 3-hour sessions.

In the first workshop, stakeholders identify key factors and collaboratively develop a visual representation of the system, illustrating various factors that influence children’s face-to-face interactions with peers during leisure time in the local area—and how these factors are interconnected. The purpose of the system map is to help stakeholders understand the system’s dynamics and support system-level change [31]. During the second workshop, and based on the system map, stakeholders identify existing actions and prioritize key leverage points for intervention. Local actions are then outlined, and action groups are formed based on individuals’ interest, motivation, and capacity to drive change within the specific area. The overall goal of the workshops is to increase opportunities for children to engage in face-to-face leisure activities with peers. This is supported by building shared awareness and understanding of the challenge that children spend more time on screens and less together in person, and fostering empowerment, a sense of unity, and supportive social networks to take collective action.

### Effectiveness Evaluation

#### Overview of Outcome Measures

All outcome measurements are conducted at all 18 schools at baseline (T0) and again after 13‐15 months. In addition, the leisure time activity questionnaire—which includes the primary outcome of time spent face-to-face with peers—is administered at T0 + [6‐10 months]. An overview of the measurements is provided in Table 2. Below, outcomes related to the primary target groups (ie, children and their parents) are detailed.

**Table 2. T2:** Overview of outcomes, measurement methods, time points, and information on data source and target (ie, the person or group the outcome concerns). The table presents the outcomes assessed at each time point, along with the corresponding measurement methods. For each outcome, the table specifies who the outcome concerns (target) and how data were collected (data source). For example, when parents report on their child’s screen use, the child is the target, and the data source is specified as parent-report. For subjective measures, the respondent is indicated; for digital measures, the source is specified (eg, app-based or device-based).

Outcome	Target	Measurement	Data source	Time points
Total time spent face-to-face with peers, time spent face-to-face with peers in different domains, and solitary screen use	Child	Leisure time activity questionnaire	Parent-report	T0, T0+(6‐10 months), and T0+(13‐15 months)
Total screen media use and screen media addiction	Child	General parental questionnaire	Parent-report	T0 and T0+(13‐15 months)
Smartphone addiction	Parent	General parental questionnaire	Parent-report	T0 and T0+(13‐15 months)
Family dynamics related to screen use	Family	General parental questionnaire	Parent-report	T0 and T0+(13‐15 months)
Physical activity and sleep	Child	Axivity AX3 triaxial accelerometer	Device-based	T0 and T0+(13‐15 months)
Smartphone time	Parent	Avicenna app	App-based	T0 and T0+(13‐15 months)
Smartphone time	Child	Built-in screen time tracking features (iOS/Android)	Device-based (retrieved by research team)	T0 and T0+(13‐15 months)
Well-being	Child	The Strengths and Difficulties Questionnaire	Teacher/pedagogue-report	T0 and T0+(13‐15 months)
Social relations and class cohesion	School class	Child questionnaire	Child-report (during school hours)	T0 and T0+(13‐15 months)

#### Children’s Time Spent Face-to-Face With Peers

To assess the primary outcome, children’s face-to-face time with peers during leisure, parents receive an SMS-based leisure time activity questionnaire about their child’s leisure activities for 7 consecutive days, followed by once-weekly messages for 7 weeks, during both the baseline and follow-up periods. Midway, they receive the same questionnaire for 7 continuous days. The questions cover the amount of time children spend in after-school clubs, organized leisure activities (eg, sports or crafts), and unorganized time with peers such as playdates. Total face-to-face interaction time with friends during leisure is calculated as the sum of these 3 categories.

#### Children’s Solitary Screen Use

As part of the SMS-based leisure time activity questionnaire, parents are asked to report on children’s time spent using screen media devices (including smartphone, tablet, television, and computer) alone. Screen time is defined as “alone” when the child is using a screen without others in the same room being actively involved in the activity. For example, online interaction with others still qualifies as alone time, whereas shared use—such as interacting together on a tablet—does not.

#### Children’s Physical Activity and Sleep

Children’s physical activity is assessed using Axivity AX3 triaxial accelerometers [32] worn at the thigh using two adhesive patches 24 hours/day for 7 consecutive days at baseline and follow-up [33]. Time spent in different intensity domains of physical activity, physical activity types, and sleep metrics is determined using the appropriate algorithms, such as those developed by Brønd et al [34]. Children with at least 3 valid weekdays and 1 valid weekend day will be considered compliant with the monitoring protocol. Preparation of the accelerometers and download of data will be conducted using the OmGui software [35].

#### Child Smartphone Time, Total Screen Media Use, and Addiction

Parents are asked to install an app on their child’s smartphone if the child owns one [36]. The app objectively monitors smartphone use over 3 weeks at both baseline and follow-up by logging screen activation and deactivation events. In addition, the research team retrieves data on children’s smartphone time from the past week as part of the assessment battery conducted during school hours at both baseline and follow-up.

Using a modified version of the SCREENS-Q [37], children’s overall screen media use is parent-reported at baseline and follow-up. Moreover, parents report their child’s screen media addiction using the Problematic Media Use Measure—Short Form (PMUM-SF) [38]. The PMUM-SF is a validated 9-item parent-report scale designed to capture addictive-like patterns of screen media use in children aged 4-11 years, based on criteria reflecting impaired control, preoccupation, withdrawal, and family conflict [38].

#### Child Well-Being

Child well-being is assessed using the Strengths and Difficulties Questionnaire for teachers, consisting of 25 items focusing on emotional symptoms, conduct problems, hyperactivity/inattention, peer relationship problems, and prosocial behavior at baseline and follow-up [39,40]. In addition, as part of the child questionnaire, children are asked to complete Cantril’s Ladder [41], a widely used single-item measure of global life satisfaction.

#### School Class, Social Relations, and Cohesion

To assess peer relationships and social structures within the school class, children are asked—as a part of a child questionnaire—to indicate which classmates they spend the most time with during recess and leisure activities. These data are used to construct sociograms, enabling analysis of social networks, including indicators such as centrality, mutual connections, and potential social isolation [42]. In addition, children will report on perceived class cohesion.

#### Parent Smartphone Time and Addiction

As for the children, parents are asked to download an app [36] to their own smartphone to track smartphone use throughout the intervention period. Smartphone addiction is self-reported using the Smartphone Addiction Scale—Short Version (SAS-SV) at baseline and follow-up [43]. The SAS-SV is a validated 10-item questionnaire designed to assess symptoms of problematic smartphone use, including daily-life disturbance, withdrawal, tolerance, and preoccupation.

#### Family Dynamics Related to Screen Media Use

As a part of the general parental questionnaire, parents are asked to report on the frequency of conflicts in the family related to screen media use.

### Process Evaluation

A comprehensive process evaluation is conducted, guided by the framework of Moore et al [44] and the program theory. The process evaluation will explore three key domains—(1) implementation, (2) mechanisms of change, and (3) context—as recommended by Moore et al [44]. The primary purpose of the process evaluation is to provide an understanding of the implementation of the intervention and relevant contextual factors. In addition, the process evaluation will enable exploration of potential mechanisms through which the intervention may influence outcomes.

All intervention components follow standardized manuals and predefined structures to support consistency across settings. Fidelity is assessed using structured facilitator checklists completed after each session (ie, facilitators of family meetings, local workshops, the after-school club development program, and teachers implementing the curricular activities), documenting whether predefined components were delivered and to what extent they were implemented as intended. Information about reach (extent of participation) and any adaptations or deviations from the protocol are also recorded by the facilitator. In addition, participants are asked to complete questionnaires immediately after participating in each respective intervention component, except for the curricular activities and the brief exercise. This together will enable us to understand how the intervention was implemented and received across different settings.

To explore mechanisms of change, we gather information about potential mechanisms identified in the program theory, including, but not limited to, perceived social support, collective agency, and actions. This information is obtained at multiple time points, depending on the component: before, immediately after, and at follow-up for the local workshops and the after-school club program; and immediately after and at follow-up for the family meetings and the educational material. To obtain a more nuanced understanding, semistructured interviews are also conducted in some cases. For example, to capture a more complete picture of actions initiated as a result of the local workshops and after-school club program, we plan to interview at least one participant per local workshop or after-school club.

To gain an understanding of the different contexts in which the intervention is implemented, we explore contextual factors (eg, organizational structures, local resources, and existing practices) that may influence implementation and outcomes. These data are collected through interviews and questionnaires targeting key informants (ie, representatives of the local community, school, and after-school club).

Based on insights from the feasibility study and in alignment with the recommendations by Moore et al [44], we recognize the need for a flexible, multimethod approach in the collection of qualitative data. While interviews are the preferred method for exploring participants’ experiences in depth, open-ended questionnaires are used when participants decline to take part in interviews or when scheduling interviews is not feasible. This approach allows participants to provide written reflections in their own words and helps ensure that perspectives from a broader range of participants are captured in the process evaluation.

### Data Management

Questionnaire data are collected using SurveyXact (Ramboll), except for the data from children (ie, child questionnaire), which is obtained through the system Klassetrivsel (Skolevisioner ApS). This platform enables the collection of information for assessing peer relationships and social structures within the school class and offers the option of having questions read aloud. All data—including questionnaire responses, audio recordings and transcriptions from interviews, and data from objective measurements—will be extracted and securely stored on servers hosted by the University of Southern Denmark. Data are stored in their raw form.

### Statistical Methods and Analysis

#### Sample Size Calculation

We anticipated a total of 1080 eligible 3rd-grade children, assuming an average of 2.5 classes per school and 24 students per class in each of the 18 schools. With an expected participation rate of approximately 80%, we aimed to enroll 864 children at baseline. Accounting for an estimated 15% dropout or missing data rate, we projected an average of 41 children per school (cluster) in the final analytical sample, resulting in a total sample size of approximately 738 children. Drawing on a previous Danish school-based study conducted by our research group [45], we assumed a coefficient of variation in cluster size of 0.24 and an intracluster correlation coefficient of 0.07. The intraclass correlation coefficient estimate was based on internal calculations from that study using a related behavioral outcome (physical activity), as direct estimates for the present primary outcome were not available. Additionally, based on findings from the feasibility trial, we estimated a correlation of 0.67 between baseline and follow-up measurements, and a standard deviation of 38 minutes per day in both the intervention and control groups. To control for type I error due to the small number of clusters, we lowered the α level to .025 in the power calculation. This adjustment was made in anticipation of applying the Satterthwaite correction for mixed linear models, as recommended for small-sample cluster trials [46]. Under these assumptions, the study is powered at 80% to detect a statistically significant mean difference of 13.5 minutes per day or more between the intervention and control groups at follow-up. A difference of 13.5 minutes per day corresponds to approximately 1.6 additional hours of peer interaction per week, roughly equivalent to one extra weekly after-school playdate or an extra organized extracurricular activity. Such changes may be meaningful, as previous research has shown that engaging in social leisure activities, including meeting friends at least once a week, is positively associated with adolescents’ well-being and perceived peer support [47]. Moreover, social connection has been consistently associated with better physical and mental health [48]. This interpretation is further supported by Danish data indicating that a substantial proportion of 11-year-olds have relatively low levels of face-to-face interaction with peers, with approximately 50% reporting that they meet friends once a week or less, or not at all [9]. Together, this supports that the chosen effect size may represent a meaningful change in children’s everyday social interaction.

#### Baseline Characteristics

Baseline characteristics will be presented descriptively for the intervention and control groups using appropriate summary statistics. In addition, the balance for the school-level covariates included in the constrained randomization procedure (number of students in 3rd grade, parental ethnicity, parental education level, and building coverage) will be reported.

To assess sample representativeness, baseline characteristics will be compared between children with at least one participating parent and those without participating parents using data available for the majority of children. These comparisons will include selected child-reported measures (eg, indicators of well-being and leisure activities), as well as teacher-reported Strengths and Difficulties Questionnaire scores.

#### Effectiveness Evaluation

##### Primary Outcome

The primary outcome is parent-reported total face-to-face interaction time with friends during leisure, assessed using the SMS-based leisure time questionnaire. The primary end point is the between-group difference from baseline to 13‐15 months follow-up.

##### Secondary Outcomes

Secondary outcomes include children’s time spent face-to-face with peers categorized into distinct time domains (after-school club, organized activities, and unstructured time with peers) and solitary screen use during leisure time assessed using the SMS-based leisure time questionnaire. Secondary end points are between-group differences from baseline to 13‐15 months follow-up.

In the clinical trial registration, 5 secondary outcomes were prespecified, including physical activity. However, due to time and resource constraints, physical activity will not be included in the primary publication and will instead be reported separately. Consequently, this outcome will be treated as exploratory. The remaining 4 secondary outcomes will be included in the primary publication alongside the primary outcome and analyzed within a confirmatory framework with appropriate adjustment for multiple testing.

##### Primary Analysis

Mixed effects regression models will be used to estimate between-group differences from baseline to follow-up in time spent face-to-face with peers. Models will be adjusted for weekday and include school, participant ID, and measurement round as random effects to account for clustering and repeated measurements. Imbalanced covariates will be included as fixed effects if relevant. The Satterthwaite correction will be applied to account for the small number of clusters, as recommended [46]. All analyses will follow the intention-to-treat principle.

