##### Sensitivity Analyses

Given that the primary outcome is ordinal, the primary analysis will be repeated using mixed ordinal logistic regression with the outcome on its original scale.

For all analyses, hypothesis tests will be 2-sided with a significance level of α=.05. Statistical analyses will be conducted using Stata or R (R Foundation for Statistical Computing).

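### The planned effect is a difference from baseline, but the model does not say how baseline enters; constraining the baseline means to be equal would give a more precise estimate

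*Protocol article*

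**What the plan says.** The hypotheses in the Introduction compare the arms on the increase, or for screen use the reduction, from baseline to follow-up. The Primary Outcome section says: "The primary end point is the between-group difference from baseline to" the 13-15 month follow-up. The Secondary Outcomes section words its end points in the same way.

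For estimation, the Primary Analysis section says: "Mixed effects regression models will be used to estimate between-group differences from baseline to follow-up in time spent face-to-face with peers". It names weekday, random effects for school, participant and measurement round, covariates found to be imbalanced, and the Satterthwaite correction. Secondary Analyses carries this approach to the four secondary outcomes.

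The Sample Size Calculation reports that "we estimated a correlation of 0.67 between baseline and follow-up measurements" and describes a detectable difference "between the intervention and control groups at follow-up". It does not say how the correlation enters the variance.

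**The concern.** Read plainly, the model treats baseline as one of the outcome rounds and takes a group-by-round contrast. If it also has a free group effect at baseline, that contrast is the difference in mean change. A change contrast subtracts the whole baseline difference, including its noise. A baseline-constrained or baseline-adjusted contrast subtracts only the part that predicts follow-up, so for the same expected effect its variance is smaller.

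The loss matters because the trial is short of its planned size. The plan assumed about 738 analysed children; Table 3 shows 343 with an enrolled parent at baseline and 351 at follow-up. Recruitment is over, so the analysis model is one of the few remaining ways to gain precision. With nine schools per arm, chance imbalance at baseline is also likely, and a change contrast handles it less well.

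**Working it through.** **Inputs** (Sample Size Calculation unless noted): SD 38 min/day, "a standard deviation of 38 minutes per day in both the intervention and control groups"; correlation r = 0.67; ICC 0.07; coefficient of variation (CV) of cluster size 0.24; 18 schools randomized 1:1, so 9 per arm; 41 children per school. On alpha, "we lowered the α level to .025 in the power calculation", in anticipation of the Satterthwaite correction. For the analysis, "hypothesis tests will be 2-sided with a significance level of α=.05" (Sensitivity Analyses).

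**Formulas.** For m children per school:
- Design effect: DE = 1 + [(1 + CV²)m − 1] × ICC
- Standard error: SE = 38 × √(f × 2 × DE / (9m))
- Change: f = 2(1 − r) = 0.660
- Constrained or adjusted baseline: f = 1 − r² = 0.551

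Using one f for the whole variance assumes that 0.67 also holds between school means.

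**1. The plan's own figure.** The claim is that "the study is powered at 80% to detect a statistically significant mean difference of 13.5 minutes per day or more". With m = 41, DE = 1 + (1.0576 × 41 − 1) × 0.07 = 3.965. The SE is 4.526 for change and 4.136 for constrained baseline. Detectable difference at 80% power (value without the CV term in brackets):

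| Variance | Reference and alpha | min/day |
|---|---|---|
| Change | t, 16 df, two-sided .05 | 13.51 (13.22) |
| Change | normal, .025 | 13.95 (13.66) |
| Constrained/adjusted | t, 16 df, .025 | 13.86 (13.57) |
| Constrained/adjusted | t, 16 df, two-sided .05 | 12.34 (12.08) |
| Constrained/adjusted | normal, .025 | 12.75 (12.48) |

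The closest match with the CV term is change, tested as planned: (2.120 + 0.865) × 4.526 = 13.51, with 80.0% power at 13.5. The adjusted variance comes close only if alpha .025 and a 16-df t are applied together, which corrects twice for few clusters. The figure therefore does not identify the formula.

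**2. Relative precision.** Variance ratio 0.660/0.551 = 2/(1 + 0.67) = 1.198; SE ratio √1.198 = 1.094.

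**3. Dependence on the school level.** The documents give no correlation between a school's baseline and follow-up means, so a range is assumed. If the true school effects correlate at s, the correlation of observed school means is ρ = [ICC × s + (1 − ICC) × r/m] / [ICC + (1 − ICC)/m], and the variance ratio is 2/(1 + ρ). With m = 41:
- s = 0.5: ρ = 0.0502/0.0927 = 0.542, ratio 1.30
- s = 0.67: ratio 1.20
- s = 0.8: ratio 1.13
- s = 1.0: ρ = 0.0852/0.0927 = 0.919, ratio 1.04

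With about 16 children per school, the ratio is 1.26-1.27 at s = 0.5 and 1.08-1.09 at s = 1.0. Each pair depends on whether 0.67 is read as the overall or the within-school correlation.

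**4. Power at the numbers enrolled** (t with 16 df as an approximation to Satterthwaite, two-sided .05, 13.5 min/day, r = 0.67 at both levels):
- 343 children, all analysed: m = 19.06, DE = 2.341. SE is 5.10 for change and 4.66 constrained. Power is 70.0% against 77.6%; detectable difference 15.2 against 13.9.
- 292 children (343 × 0.85, borrowing the planned 15% loss): m = 16.2, DE = 2.13. SE is 5.27 and 4.82. Power is 67.1% against 74.9%; detectable difference 15.7 against 14.4.

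**The case against.** The strongest reply is that the criticised model is inferred. The Primary Analysis section does not say whether a baseline group effect is fitted, whether baseline means are constrained, or whether baseline is a covariate. Its list is plainly not exhaustive, since even the group term is unnamed. The wording fits a constrained model, whose group-by-round coefficient is also a difference from baseline to follow-up. Fixed-effects coding may sit in an analysis plan that is not shown. This stands, and it is why the point is conditional on free baseline means. A difference in change is also unbiased under randomization and matches the hypotheses, so nothing here is an error of validity. Constrained randomization and covariate adjustment already deal with part of any imbalance.

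A reader might infer that the power calculation assumed baseline-adjusted efficiency which the analysis then gives up, because it speaks of a difference at follow-up and uses r. The documents do not support that. Both formulas use r, none is named, and 13.5 min/day is reproduced at least as well by a change variance.

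A reader might also take the 20% as fixed and the remedy as free. Neither holds. The gain shrinks to 4-9% if school effects are constant over time. The constraint leans on a covariance model estimated from 18 schools, and on baseline days preceding the release of allocation. Adjusting follow-up days for each child's baseline mean is not an interchangeable alternative. It drops children without baseline data unless these are imputed, whereas Missing Data admits anyone with one valid day and Results reports 32 children who joined after baseline.

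**Conclusion.** The point holds as a recommendation on precision. The effects are worded as differences from baseline, and the stated terms name neither baseline adjustment nor a common baseline mean. If baseline means are left free, the variance is about 20% larger than it need be at r = 0.67 on both levels. It is 26-30% larger at an assumed school-level correlation of 0.5, and 4-9% larger at 1.0. The power gain of about 8 percentage points (70% to 78%, or 67% to 75%) belongs to the 0.67 case and rests on the protocol's SD, ICC and CV. It does not make up for low enrolment: power stays below 80% at 13.5 min/day in both cases. The equality constraint is reasonable because schools were randomized and, under Study Design and Participants, allocation was released after each school's baseline assessment. No mismatch with the sample size calculation is established.

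**What to change.** Before the effect analysis starts (the article says it had not begun as of March 2026), specify a constrained longitudinal mixed model. Use fixed effects for round and for group by post-baseline round, with no group main effect at baseline, plus weekday as planned. Include school-by-round and child random effects, so that the school effect is not forced to be constant over time. Take the 13-15 month group coefficient as the primary estimate and use the same model for the four secondary outcomes. Prefer this to adjusting follow-up days for the child's baseline mean, because it keeps children without baseline data. State that only days before a school's allocation was released count as baseline, and state which variance formula lies behind 13.5 min/day.

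The cost is analysis-plan wording and no new data. The small downside is reliance on the covariance model with 18 schools and on the timing of baseline days.
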